### Monitoring

The GEMS Trial Steering Group will be responsible for the conduct of the trial. An independent Monitoring Committee, with established terms of reference, will monitor the study processes and review the serious adverse events reported by the sites.

### Analysis and reporting of results

Baseline characteristics of all women randomised will be summarised descriptively by the study group allocated at randomisation, Lower Criteria Group and Higher Criteria Group, to assess comparability of the randomised groups. Treatment evaluations will use the intention-to-treat principle. Statistical tests will be two-sided and maintained at the 5% level of significance. Both unadjusted and adjusted analyses will be carried out. Secondary exploratory analyses will consider baseline covariates that show evidence of imbalance between study groups and are related to the outcome of interest. The risk estimates and 95% confidence intervals will be reported using log binomial regression for binary outcomes. Continuous outcomes will be analysed using linear regression. Statistical significance will be assessed at the 0.05 level using a two-sided comparative test.

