There has been considerable uncertainty [16, 18, 23] and significant ongoing debate [24–27] as to whether to adopt the IADPSG diagnostic criteria. A major concern is the greatly increased proportion of pregnant women who would be diagnosed with GDM. Although the exact increase in rate will vary by country, estimates for New Zealand [28] and similar populations suggest a two to three fold increase. Using the average HAPO rate of 17.8%, adopting the new criteria in New Zealand would more than double [28] the number of women diagnosed with GDM each year from 5,500 to over 11,000 women [2, 22]. For women ‘labelled’ as GDM there are personal costs and potential harms from increased obstetric and neonatal interventions, such as induction of labour, caesarean birth, and increased surveillance for and treatment of neonatal hypoglycaemia. Nevertheless, applying the IADPSG lower diagnostic threshold may reduce serious maternal and/or perinatal complications and later metabolic disease in both women and their offspring.

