### Trial entry, randomisation and allocation of the study group

Potentially eligible women will be offered participation in the GEMS Trial when considering their treatment options for testing for GDM in mid-pregnancy. They will be provided with information about the trial by their health professional or the research personnel and counselled about the study. All consenting women will have a 75 g OGTT with plasma glucose concentrations determined on fasting, and at 1 and 2 hours. After their OGTT, eligible women will be randomised by the research assistant, at a ratio of 1:1, using a central computerised system into one of two study groups: either the *Lower Criteria Group* or the *Higher Criteria Group* (Fig. 1)

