### Generation of the sequence to which participants will be randomised

The central randomisation service will use a randomisation schedule with balanced variable blocks, prepared by an investigator not involved with recruitment or clinical care, using a randomisation table created by computer software. Stratification will be by body mass index (BMI, < 25 and ≥ 25 kg/m^2^) and by planned birthing institution.

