### Sample size

For the primary outcome of LGA, a trial of 4,158 women will be able to show a 2.9% absolute risk reduction from 12.9% with current New Zealand criteria [15, 21] to 10.0% using the new IADPSG criteria [19], (α = 5%, two-tailed, 80% power, 10% loss to follow up), based on HAPO [22] and LGA rates from unpublished information from the ACHOIS Trial [11].

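### The whole-cohort comparison should stay primary, but care differs by arm for only about 9% to 12% of women on the article's own figures, so a randomised analysis of those women should be pre-specified (or confirmed) before unblinding

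*Protocol article*

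**What the plan says.** All references are to the protocol article.

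- **Trial entry, randomisation and allocation of the study group:** "All consenting women will have a 75 g OGTT with plasma glucose concentrations determined on fasting, and at 1 and 2 hours". Allocation comes afterwards: "After their OGTT, eligible women will be randomised by the research assistant, at a ratio of 1:1".
- **Treatment schedules:** a woman normal by her allocated criteria has routine care, and a woman positive by them has standard GDM care. Lower is positive at fasting ≥ 5.1, 1 h ≥ 10.0 or 2 h ≥ 8.5 mmol/L. Higher is positive at fasting ≥ 5.5 or 2 h ≥ 9.0 mmol/L. Women, their health professionals and those collecting outcomes are blind to the allocated criteria.
- **Generation of the sequence:** "Stratification will be by body mass index" and by planned birthing institution. OGTT result is not a stratum.
- **Sample size:** "a trial of 4,158 women will be able to show a 2.9% absolute risk reduction from 12.9"% "to 10.0% using the new IADPSG criteria", with "α = 5%, two-tailed, 80% power, 10% loss to follow up".
- **Analysis and reporting of results:** "Treatment evaluations will use the intention-to-treat principle". Unadjusted and adjusted analyses are both planned. Exploratory analyses consider covariates that turn out imbalanced and are related to outcome. No analysis by OGTT category is mentioned.
- **Background, on the choice of threshold:** "Using the average HAPO rate of 17.8%, adopting the new criteria in New Zealand would more than double" the number diagnosed each year. Estimates for New Zealand and similar populations are put at a two- to three-fold rise.

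**The concern.** The Higher thresholds lie above the Lower ones, so every woman positive on Higher is also positive on Lower. That gives three zones: normal on both, between (positive on Lower only), and positive on both. In the first and third zones the two arms prescribe the same care, and blinding leaves no evident route to an arm effect. Any effect of moving the threshold arises in the between zone, while the comparison described averages it over everyone.

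The Discussion expects the trial to establish which criteria give most benefit. If treatment helps the additional women appreciably but they are about one in ten, the overall difference will be small and probably non-significant, and could be misread as no benefit to them. Harms that the Background fears for newly labelled women, such as induction and caesarean birth, are diluted in the same way. The zone is known for each woman before allocation, so a randomised comparison in the women concerned needs no new data. Introduced after unblinding, it would carry only post hoc weight.

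**Working it through.** **1. The plan's own figure.** The inputs are 12.9% v 10.0%, two-sided 5%, 80% power and 10% loss (Sample size). The pooled-variance two-proportion formula gives 1,892 per arm, or 3,784 evaluable, and 3,784 / 0.9 = 4,205. The stated 4,158 is within 1.1%. Evaluable women at 4,158: 4,158 × 0.9 = 3,742, or 1,871 per arm, with power 79.6%. The stated size therefore reproduces.

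**2. Share of women whose care differs.** f = L × (1 − 1/k), where L is the share positive on Lower and k the ratio of Lower to Higher diagnoses. Applying the Background's 17.8% and two- to three-fold figures to trial women is an assumption.

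| L | k | f | Dilution 1/f |
|---|---|---|---|
| 17.8% | 2 | 8.9% | 11.2 |
| 17.8% | 3 | 11.9% | 8.4 |
| 25% (assumed) | 2 | 12.5% | 8.0 |
| 25% (assumed) | 3 | 16.7% | 6.0 |
| 35% (assumed) | 2 | 17.5% | 5.7 |
| 35% (assumed) | 3 | 23.3% | 4.3 |

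The first two rows mean about 370 to 493 of the 4,158 women.

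**3. Power in the stratum and in the whole cohort.** Evaluable stratum size per arm is 1,871 × 0.089 = 167 to 1,871 × 0.119 = 223. The difference over all women is f × (p_C − p_T), where p_C and p_T are LGA rates in the stratum under Higher and Lower allocation. Whole-cohort power takes 12.9% less that difference against 12.9%, with 1,871 per arm.

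Power = Φ{[d√n − 1.96√(2p̄(1 − p̄))] / √(p₁(1 − p₁) + p₂(1 − p₂))}, with d the difference, n the number per arm and p̄ the mean of p₁ and p₂.

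The article gives no LGA rate for this stratum, so the control rates below are assumed. The ratio 0.775 is 10.0/12.9 from the Sample size section, carried over to the stratum as an assumption.

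| LGA in stratum, Higher v Lower | Risk ratio | Stratum power | Whole-cohort power |
|---|---|---|---|
| 20% v 10% | 0.5 | 73% to 84% | 13% to 20% |
| 25% v 12.5% | 0.5 | 84% to 92% | 18% to 28% |
| 30% v 15% | 0.5 | 91% to 97% | 24% to 39% |
| 20% v 15.5% | 0.775 | 19% to 24% | 6% to 7% |
| 25% v 19.4% | 0.775 | 23% to 30% | 7% to 9% |
| 30% v 23.2% | 0.775 | 29% to 36% | 8% to 11% |

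Example: 20% v 10% at f = 8.9% is 0.089 × 10 = 0.9 points over all women, and 0.119 × 10 = 1.2 points at f = 11.9%.

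**4. Validity of the restricted comparison.** The zone is fixed by a test done before allocation. Comparing allocated arms within it preserves randomisation and is itself an intention-to-treat analysis.

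**The case against.** Much of the opposing case stands.

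- **The intention-to-treat sentence is not an error.** The primary hypothesis concerns using one set of criteria rather than another. That is a policy comparison, its population is everyone tested, and dilution is part of that estimand. A reader might infer that pooling all women is the wrong analysis; the stated hypothesis does not support that.
- **Absence cannot be asserted.** A reader might infer that the trial has no analysis of the between-criteria women. The article condenses a fuller protocol, and neither that nor any SAP is shown. Subgroups, covariate lists and testing order are commonly left to them. All that can be said is that the article describes no such analysis and does not stratify on OGTT zone.
- **The dilution is derived.** A ten-fold figure might be read as a property of this trial. It applies an average HAPO rate and a population estimate to women selected in part by excluding previous GDM. At an assumed prevalence of 25% to 35% the factor is about 4 to 8.
- **The stratum analysis may not settle the question.** The high power figures all assume that LGA halves. At the plan's own relative effect, power is about 19% to 36%. For the infant and maternal composites no power can be claimed.
- **Stratifying by zone is not needed.** Randomisation already makes the comparison valid among several hundred women.

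What survives is narrower. In every scenario examined, the restricted comparison has more power than the pooled one to detect an effect confined to these women, and it estimates that effect directly.

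**Conclusion.** This is an inexpensive improvement to a valid plan. The whole-cohort comparison should remain primary. On the article's own figures, only about 9% to 12% of women would receive different care by arm (about 12% to 23% at the higher assumed prevalence), so a null overall result would be weak evidence about the women whose diagnosis changes. A pre-specified comparison in that stratum is fully randomised and uses data already collected.

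The conclusion rests on three assumptions: that the Background prevalence figures carry over to trial women, that concordant women have no arm effect, and, for power, the assumed LGA rates. The structural point, that care differs only in the between zone and that the zone is known before randomisation, rests on the stated thresholds and sequence alone.

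**What to change.** Before unblinding:

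1. Keep the whole-cohort intention-to-treat comparison as primary.
2. Pre-specify, or confirm if the SAP already has it, one key secondary analysis: LGA by allocated arm among women positive on Lower and negative on Higher, with the arm-by-OGTT-zone interaction and a stated place in the testing order after the primary.
3. Report the infant and maternal composites in the same women as supportive, without a power claim.
4. Name OGTT zone (normal on both, between, positive on both) as a covariate in the adjusted primary model, in addition to any covariate considered because of observed imbalance.
5. State power for the stratum analysis as a range that includes the unfavourable end.

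Stratifying randomisation by OGTT zone is optional.

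The cost is a paragraph of text, one more test in the hierarchy and limited power for modest effects. No new data are needed.

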## Discussion

Gestational diabetes is a significant and increasing health problem globally that has a major, negative effect on maternal and perinatal health, with lifelong consequences. Women with GDM are at higher risk of pre-eclampsia, more likely to have their labour induced and to give birth by caesarean section than women without GDM [4]. Their lifetime risk for developing type 2 diabetes and cardiovascular disease is high [5, 6]. Infants born to women with GDM are more likely to be LGA than infants born to women without GDM, with increased risk of an operative birth, birth injuries, and significant neonatal morbidity. Children born to women with GDM are at increased risk of being obese, developing high blood pressure and type 2 diabetes [7, 9, 37]. Treatment of women with GDM with dietary and lifestyle advice reduces adverse maternal and perinatal outcomes [11, 12] but there is still uncertainty, because of a lack of high-quality evidence, as to the optimal, diagnostic criteria to use for the diagnosis and treatment of GDM.

The GEMS Trial is assessing two diagnostic thresholds for GDM, the currently used, higher diagnostic criteria [15, 17] and the IADPSG, lower diagnostic criteria [19] for their effects on fetal growth, perinatal morbidity, maternal physical and psychological morbidity, and health service utilisation. The GEMS Trial results will establish which of these diagnostic criteria provides most benefit for maternal and infant health.

The results of the GEMS Trial will be directly relevant to the health needs of pregnant women and their infants and will provide the needed information to guide clinical practice and health policy for best care of women with GDM and their infants in New Zealand with relevance globally.

## Abbreviations

BMI: Body mass index
GDM: Gestational diabetes mellitus
OGTT: Oral glucose tolerance test
